## Abstract

**Background:**

Mental health difficulties in preschool children often go unnoticed and may result in delayed access to potentially beneficial services. In Norwegian kindergartens, teachers get to know the children well over time and have parent-teacher conferences once or twice a year. Kindergarten is thus a well-suited arena for early identification and intervention of mental health difficulties. To address the need for a kindergarten-specific method for secondary prevention, we have developed Dialogue-Based Early Detection (DBED) in close collaboration with educators and parents in eight different kindergartens. Results from a feasibility study indicate that DBED works well as a parent-teacher collaborative screening method and is well accepted by the users. In the PRO-DIALOG project, we will examine the potential of DBED and explore its possible long-term effects in a randomized controlled trial.

**Methods:**

Ten kindergartens will be randomly selected to implement DBED, while ten will act as controls, offering ordinary parent-teacher conferences. Parents of at least 100 + 100 children will be recruited. The primary outcome will be children’s mental health in the intervention group as assessed by the Strengths and Difficulties Questionnaire (SDQ), during the 5-year follow-up, compared to the control group. Secondary outcomes will be (i) the effect of DBED on parental stress as measured by the Parental Stress Scale (PSS) and (ii) time to activation of support, as measured by the duration from the first parent-teacher conference to activation of any support, comparing the two groups. We will also assess (iii) socio-demographic predictors for mental health development, parent and teacher concern for the child, parental stress, and parent satisfaction with DBED, (iv) screening properties of DBED compared to SDQ, and (v) social validity of DBED as measured by user-satisfaction questionnaires and interviews with both parents and teachers.

**Discussion:**

This complex intervention study includes a wide range of outcomes beyond the mental health scores of kindergarten children. If the intervention is well accepted and has a positive influence on the children’s mental health, the DBED method has a potential for a wide dissemination. This study will produce new knowledge on kindergarten as an arena for the promotion of mental health among young children.

**Trial registration:**

ClinicalTrials.gov NCT06471816. Registered on 2024–06-22 16:06. Retrospectively registered.

**Supplementary Information:**

The online version contains supplementary material available at 10.1186/s13063-025-08980-x.

## Administrative information

Note: the numbers in curly brackets in this protocol refer to SPIRIT checklist item numbers. The order of the items has been modified to group similar items (see http://www.equator-network.org/reporting-guidelines/spirit-2013-statement-defining-standard-protocol-items-for-clinical-trials/)

## Introduction

### Background and rationale {6a}

Childhood mental health has been proposed to be the strongest predictor of adult well-being [1]. The major costs of common mental health problems among children both for the individual and society are well known, and there are negative effects on mental and physical morbidity, alcohol and substance abuse, crime, relational problems, injuries, suicide, social, peer, and school-related problems, and sick leave [2, 3]. Early detection and intervention are therefore likely to be important to prevent secondary consequences of mental health problems, and early intervention may reduce socio-economic costs in the long run [4].

Ideally, all children with significant emotional, behavioral, or cognitive problems should be detected and offered adequate developmental support tailored to individual needs. Such support could be provided by community-level agencies or by child and adolescent mental health services (CAMHS), depending on the need. The help should be given as early as possible to support positive development, promote well-being, and achieve optimal educational and social gain.

Nevertheless, only a minority of children at risk is detected and offered appropriate interventions, younger children less often than older ones [5–8]. In Norway, most children (> 95%) attend a kindergarten from the age of 1 year. Law regulates the educational standards in the kindergartens, including requirements for staff and educational competence. Consequently, kindergartens are well suited for first-line detection and intervention for better mental health for children in general [9]. However, established screening programs for behavioral or emotional problems among children have been criticized by some users, i.e., kindergarten teachers and the parents of the children, for pathologizing natural variation in behavior and emotional reactions and for generating unnecessary concern for healthy children.

In the absence of a generally accepted screening tool adapted to ordinary kindergartens, we developed the Dialogue Based Early Detection (DBED) [10] as a specific mental health intervention for early years. After having achieved good feasibility data, we will now test its effectiveness in an RCT.

### Objectives {7}

The primary objective is to evaluate DBED’s impact on mental health for children in kindergarten measured by the Strength and Difficulties Questionnaire (SDQ) scores. However, for a better understanding of potential mechanisms, secondary objectives are to evaluate how DBED influences parental stress and activation of interventions for mental health concerns, to establish the screening properties of DBED to detect mental health problems among children in kindergarten, and evaluate its acceptability for kindergarten teachers.

### Trial design {8}

The study design is a cluster randomised open trial, where 20 kindergartens will be randomised to either DBED intervention (*n* = 10) or control groups (*n* = 10). In the control group, parent-teacher appraisals are performed in the traditional way (treatment as usual; TAU). Children’s mental health, as measured by SDQ scores, will be assessed by both parent- and teacher-report biannually through the last 3 years in kindergarten and for the first 2 years in school. Our analyses will examine DBED’s possible superiority to TAU. Similar analyses will be performed as to DBED’s impact on activation of interventions for mental health concerns and parental stress.

The number of components involved, the wide variety of behaviours targeted, expertise and skills required by those delivering the intervention, and the permitted level of flexibility of the intervention confirm that the PRO-DIALOG project is complex intervention research [11]. Hence, in addition to the core trial design, we will use a mixed-method approach to the process evaluation, including both quantitative and qualitative methods. A logic model of the project can be found in Additional file 1.

## Methods: participants, interventions and outcomes

### Study setting {9}

The participating kindergartens are all localized in Bergen or Øygarden municipalities, Norway, with approx. 290,000 and 40,000 inhabitants, respectively. These municipalities cover a mix of urban and sub-urban areas with no generally underprivileged localities. The kindergartens are managed by Haukeland University Hospital, Eventus barnehage AS, or Øygarden municipality.

### Eligibility criteria {10}

Inclusion criteria: Kindergartens owned by either Haukeland University Hospital, Eventus Barnehage AS, or Øygarden municipality, each of which offer regular parent-teacher conferences. Parents of children who are beginning their third last year of kindergarten attendance. This corresponds to children born 3 years prior to the inclusion year (i.e., children born in 2021 will be recruited in the autumn of 2024).

Exclusion criteria: Kindergarten manager rejecting invitation to participate. Parents who do not understand either Norwegian or English.

### Who will take informed consent? {26a}

Study coordinator will obtain informed consent digitally from trial participants through EasyTrial. When the consent is distributed to the participants, they will have to read through the document before they choose to sign or decline. To ensure that the correct person gives consent, each participant must sign with an eSigning solution connected to their social security number. Participants may withdraw their consent whenever they wish and without explanation.

### Additional consent provisions for collection and use of participant data and biological specimens {26b}

N/a.

## Interventions

### Explanation for the choice of comparators {6b}

DBED is a novel approach to the mandatory, though loosely defined, parent-teacher conference in kindergartens. Hence, the control condition (comparator) will be a traditional parent-teacher conference (“treatment as usual”). In a qualitative part of the PRO-DIALOG project, sound recording of parent-teacher conferences from both intervention and control kindergartens will be made to analyze and compare content and communication patterns.

### Intervention description {11a}

#### Intervention

DBED [10] is a 3-step method (Fig. 1) starting with both parents and kindergarten teachers completing the Early Worry Questionnaire (EWQ) (Step 1) as a preparation for the biannual parent-teacher conference. The EWQ contains 37 questions that systematically map possible concerns for the individual child’s wellbeing and development. When a concern is stated, the respondents are asked to suggest possible causes in an open-ended follow-up question. Step 2 is the parent-teacher conference where they compare their answers from the EWQ and discuss whether there is a reason for concern or not. In case of consensus of concern, a discussion of possible further actions should follow (Step 3), such as closer observation of the child, simple educational interventions (e.g., playgroup), or referral to more specific external assessment or services. During feasibility testing (*N* = 153) of the method, DBED was well accepted by parents and teachers [10]. Preparation before parent-teacher conferences by completing the EWQ facilitated a more active involvement of the parents in the dialogue. They also more often presented previously unspoken concerns for their child [10].

**Fig. 1 Fig1:**
[figure not shown]
The steps of dialogue-based early detection

### Criteria for discontinuing or modifying allocated interventions {11b}

The intervention is not designed to be modified or personally tailored outside the decision-making process at step 2.

### Strategies to improve adherence to interventions {11c}

The DBED is a semi-structured procedure for the parent-teacher conference. Kindergarten teachers and parents have been strongly involved in the development of DBED to achieve a user-friendly method. Managers of each kindergarten are accountable for adherence to the method. The project group has provided oral and written information about the purpose and procedures of the project to both teachers and parents. Every teacher has been equipped with their own tablet for completing questionnaires and communication with the project coordinator. The online digital questionnaires have been piloted for user optimization ahead of full-scale implementation of the project. After each half-year round of parent-teacher conferences and questionnaire completion, the project group arranges digital meetings with the teachers for feedback on their experiences. The project coordinator responsible for issuing and receiving the questionnaires will remind the separate kindergarten teacher when questionnaires are not returned in time. The completeness of the submitted EWQs and conclusions from the parent-teacher conference will indicate adherence.

### Relevant concomitant care permitted or prohibited during the trial {11d}

The intervention kindergartens should not perform traditional parent-teacher conferences in addition to the DBED for the participating parents.

### Provisions for post-trial care {30}

N/a: Due to the nature of the intervention (parent-teacher conference), adverse effects from trial participation are considered unlikely. The possible actions concluded during the DBED are all part of the standard supportive measures and care and identical to those initiated in the control kindergartens (and all other kindergartens in the same municipality).

### Outcomes {12}

Primary outcome:

Effect of DBED on mental health measured as the difference between intervention group and control group in Total difficulties score of SDQ. Measurement scores will be recorded every sixth month during the entire 5-year project period (i.e., child-age 3 to 8 years) as repeated measures. SDQ sub-scores and two impact scores (difficulties in general and impact on four areas of daily functioning) will be analyzed. The primary endpoint will be during the last 3 months in kindergarten before the child starts school, giving total change over six time points of measurements. The secondary endpoint will be during the last 3 months in the second school year (10 time points of measurements).

Secondary outcomes:

Effect of DBED on time to initiated locally available supportive action analyzed as the difference in time (months) from inclusion to activation of such actions between the intervention group and control group as mean time (months) from inclusion to activation of such actions. This outcome will indicate if DBED may lead to earlier supportive actions for children.Effect of DBED on parental stress analyzed as the difference in total scores of the PSS between the intervention group and the control group [12]. Measurements will be recorded every sixth month during the project period. This outcome will indicate if DBED may lead to less or more parental stress and more or less self-confident parents.

Process outcomes:

The factor structure of EWQ as reported by parents and teacher, respectively, prior to the parent-teacher conference and as reported DBED concluded concern from the parent-teacher conference, primarily at baseline, but also at the following half-year registrations for comparative reasons.Agreement between (i) reported concern and DBED concluded concern, respectively, measured by total EWQ score and EWQ sub-scores, and (ii) mental health measured by SDQ Total difficulties score, each sub-scale score, and two SDQ impact scores, respectively, at baseline.Agreement between parent’s and teacher’s mental health report measured by agreement between parent and teacher SDQ scores and the above mentioned SDQ impact scores at baseline and after 12, 24, and 36 months, respectively.Agreement between parents and teacher in possible concerns for the child measured by percentage of EWQ items rated as the three different response options, respectively (satisfied; a bit uncertain; concerned), at baseline and after 12, 24, and 36 months, respectively).Change from reported to concluded concern during the parent-teacher conference measured similarly as the preceding outcome.Satisfaction with the DBED after all parent-teacher conferences measured by the study-specific satisfaction questionnaires for parents and teachers, respectively.Predictors of mental health change during the 5-year follow-up. Mental health is measured by SDQ-scores (Total difficulties score, sub-scales and impact scores) and the predictors (at baseline) are measured by:◦ Parent’s educational level◦ Satisfaction with economic situation◦ Social support◦ Single parenting◦ Close relatives in the vicinity◦ Norwegian language at home?◦ Is Norway parent’s country of origin?◦ Major illness or handicap◦ Level of parental concern◦ Level of teacher concern◦ Level of DBED concluded concern◦ Parent-teacher agreement after the parent-teacher conversation at baseline◦ Level of parental stressPredictors of parental and teacher concern, respectively. Concern is measured by parent and teacher EWQ total score at baseline and changes throughout the 3-year follow-up period in kindergarten, and the predictors are the same as for mental health change.Predictors of parental stress. Parental stress is measured at baseline and changes throughout the total follow-up period of 5 years, and the predictors are the same as for mental health change (except parental stress).Predictors of parent satisfaction. Parent satisfaction is measured by the study-specific satisfaction questionnaire at baseline and changes throughout the 3-year follow-up period in kindergarten, and the predictors are the same as for mental health change.

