## Assignment of interventions: blinding

### Who will be blinded {17a}

N/a: This is an open-label trial.

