## Data collection and management

### Plans for assessment and collection of outcomes {18a}

Data from the study will solely be collected by online digital questionnaires completed by teachers and parents via PC, tablet, or smartphone. The questionnaires are built on the EasyTrial platform [13] and will be distributed and collected by the study coordinator at Research Unit for Health Surveys [14]. Questionnaires are distributed by SMS (parents) or work e-mail (teachers) where a personal link to the questionnaire is attached. The answers are directly transferred to the EasyTrial platform.

All kindergarten teachers will be informed about the complementing procedures, and every questionnaire will contain instructions for users. Teachers in the intervention kindergartens are trained in the DBED procedure by a training session involving practical role-play.

The following questionnaires are used:

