## Statistical methods

### Statistical methods for primary and secondary outcomes {20a}

Primary outcome:◦ Possible differences between children in intervention and control kindergartens in mental health trajectories will be estimated by Latent growth curve (LGC) models (gives equal results as linear mixed/multilevel models, given similar parameter specification). Both random intercept fixed slope and random intercept random slope will be analyzed, meaning models with no variance in change (slope) and models with individual differences in slope (random effects). Then the full unstructured matrix with random intercept, random slope, and the covariance between intercept and slope will be tested. Initially, linear change over time will be tested. If not supported with data, different non-linear change models will be explored (quadratic, cubic, piecewise growth). Then, substantial predictors will be entered into the model and analyzed. Also, within level residual structures will be tested.Secondary outcomes:◦ Possible differences between children in intervention and control kindergartens in parental stress and time to initiated locally available supportive action, respectively, will be analyzed in a similar way to the primary outcome.Process measures:◦ Factor structure will be estimated by confirmatory factor analysis (CFA).◦ Agreements between:▪ Reported concern (EWQ) and DBED concluded concern (EWQ), respectively, and mental health (SDQ): correlations (Pearson’s and Spearman), Cohen’s (weighted) Kappa, CFA: uni-, bi-, and tri-factor models representing different sources of information (parent 1, parent 2, teacher. Latent difference score (LDS) models will also be explored for common levels and differences within and between families.Parent’s and teacher’s mental health report (SDQ): correlations (Pearson’s and Spearman), CFA, including method factors, LDS models.Parents’ and teacher’s possible worries for the child: Cross table with chi-quadrat test, Cohen’s weighted Kappa, CFA, and LDS models.▪ Change from reported (EWQ) to concluded concern (EWQ) during the parent-teacher conference: cross table with chi-quadrat test, Cohen’s weighted Kappa, CFA/LDS models.▪ Satisfaction with DBED:Initial: distribution of scores and mean values of each item. Mean value of total score.Follow-up: repeated measures of mean values of each item and total scores and LGC models.▪ Predictors of mental health change, parent concern, teacher concern, parent satisfaction, parental stress: LGC models with predictors (conditional LGC models).Statistical principles◦ Level of statistical significance: We will use the threshold of *p* = 0.05 for the main analysis. However, the threshold perspective has been debated, and there is considerable literature claiming another perspective as a relevant alternative. This implies the use of exact p-values as a degree of certainty of the generalization from sample to population. In the exploratory part of the project, this practice will be used. In addition, we will calculate effect sizes to evaluate the results beyond statistical significance.◦ Adjustment for multiplicity: Detailed power analysis (Monte Carlo analysis) was used to decide sample size for satisfactory power. Adjustment is irrelevant for this analysis. Regarding other statistical analyses, analyses may introduce risk for Type 1 errors when testing family-wise tests. When testing specific hypotheses (see above), no adjustment should be necessary. When exploring differences and relations not pre-specified in hypotheses (family wise tests), Bonferroni corrections will be used.◦ Confidence intervals to be reported: 95%◦ Methods used for assumptions to be checked for statistical methods: Residuals will be saved and checked for normality and homoscedasticity. Relations will be plotted and linearity in relations evaluated.◦ Details of alternative methods to be used if distributional assumptions do not hold: Bootstrapping will be used if normality does not hold. However, larger samples are robust for such deviations.If survival models (Cox and non-proportional parametric hazard models based on Weibull distribution), the proportional assumption will be tested. In addition, covariates will also be tested as time-dependent covariates to explore whether they relate to events differently over time.

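### The 10-wave analysis to the end of second school year crosses a break known in advance at school entry, but the plan tries a single straight line first and lets the data choose any other shape

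*Protocol article*

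**What the plan says.** The Outcomes section places the primary endpoint at the end of kindergarten, "giving total change over six time points of measurements". It then adds: "The secondary endpoint will be during the last 3 months in the second school year (10 time points of measurements". Call the six kindergarten measurements waves 1-6 and the four school measurements waves 7-10.

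The participant timeline marks DBED and TAU at waves 1-6 and at none of waves 7-10. SDQ is marked at all ten. Trial design says that SDQ "will be assessed by both parent- and teacher-report biannually through the last 3 years in kindergarten and for the first 2 years in school". School-age teacher reports must therefore come from other teachers. The article does not say so in words; it is an inference.

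Only one arm's kindergarten teachers receive the method training: "Teachers in the intervention kindergartens are trained in the DBED procedure by a training session involving practical role-play". On blinding the article says "N/a: This is an open-label trial".

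The rule for the shape of change in the statistical methods section is: "Initially, linear change over time will be tested. If not supported with data, different non-linear change models will be explored (quadratic, cubic, piecewise growth". It fixes no break at school entry and makes no distinction between the 6-wave and 10-wave analyses.

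**The concern.** The stated reason for following the children into school is to explore long-term effects. The question at wave 10 is whether a difference built up in kindergarten lasts or fades once DBED has ended. A straight line per arm ties the school years to the kindergarten years: the same rate of change must hold while DBED runs and for two years after it stops. The date at which that assumption may fail is known now, so the data need not be asked to find it.

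Teacher report adds a second difficulty. If DBED-trained teachers rate differently from control teachers, that difference ends when the children leave kindergarten. It ends at the same moment as DBED, so the teacher series cannot separate a change of rater from a change in the child.

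**Working it through.** **Inputs.** Ten half-yearly waves, coded t = 0 to 9 and taken as equally spaced (Outcomes, timeline). The break lies between t = 5 and t = 6. The plan gives no figure for the 10-wave endpoint. Its power calculation covers six outcome variables and a difference of -0.8 (Sample size), so -0.8 serves here only as the scale. Reaching -0.8 at wave 6 means -0.8/5 = -0.16 per interval.

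**Method.** Fit a least-squares line to the between-arm difference D(t). Mean t = 4.5 and Sxx = 82.5. Slope b = Σ(t - 4.5)D(t)/82.5. Change over the period = 9b. Fitted difference at wave 10 = mean D + 4.5b.

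**Effect sustained at -0.8.** ΣD = -2.4 - 3.2 = -5.6. ΣtD = -8.8 - 24 = -32.8. Then b = (-32.8 + 25.2)/82.5 = -0.0921.

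**Effect fading evenly to 0 at wave 10.** ΣD = -2.4 - 1.2 = -3.6. ΣtD = -8.8 - 8.0 = -16.8. Then b = (-16.8 + 16.2)/82.5 = -0.0073.

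**No true effect; DBED teachers score d higher than control teachers at waves 1-6 only.** b = (15 - 27)d/82.5 = -0.1455d.

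| Scenario | True wave-10 difference | Line: change over period (9b) | Line: fitted at wave 10 |
|---|---|---|---|
| Sustained | -0.8 | -0.83 | -0.56 - 0.41 = -0.97 |
| Fades evenly to 0 | 0 | -0.07 | -0.36 - 0.03 = -0.39 |
| Teacher shift d, no effect | 0 | -1.31d | 0.60d - 0.65d = -0.05d |

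The two readings of the line fail in different places. Under fading, the change over the period is about right and the fitted wave-10 value is wrong. Under a teacher shift, it is the reverse. The article speaks both of a difference between groups and of total change, so either reading could be reported.

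**Scale of d.** A false change of -0.8 needs d = 0.8/1.31 = 0.61. This is a threshold, not an estimate. Assume a random intercept, no random slope, 25% gradual dropout and residual variance 5, 10 or 15 out of 30.25 (the plan does not state it). The 10-wave slope would then be significant with probability about 63%, 37% or 27% at d = 0.61, or 21%, 13% or 10% if parent and teacher scores were averaged.

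**Would the data-driven rule catch it?** Under the same variance assumptions, with 75 to 100 children per arm and complete waves, an arm-by-curvature test (quadratic, or a knot at wave 6) has 24-73% power against the fade and 6-12% against the 0.61 shift.

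**With a change of slope fixed at wave 6.** Sustained: slopes -0.16 and 0, wave 10 = -0.8. Fade: slopes -0.16 and +0.20, wave 10 = -0.8 + 4(0.20) = 0. Both are exact. For the teacher shift, the knot alone gives slopes -0.071d and -0.247d, a change of 5(-0.071d) + 4(-0.247d) = -1.34d. It does not remove the artefact, which is why teacher waves need separate treatment.

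**The case against.** The strongest reply has four parts.

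- **The endpoint is defined by time.** The Outcomes section locates it in the last months of the second school year and defines the outcome as the difference between arms. It does not say that a slope is the estimand. This stands, and it means that the fix is close to the plan's wording.
- **Piecewise growth is already named, and knot placement is often left to a later analysis plan.** The first half is true. The objection here, however, is to a rule that the article does state: linear first, other shapes only if the data demand them. The power figures above suggest that a straight line would often survive.
- **The rater changes in both arms.** This stands. A shift common to both arms cancels. The article describes training in the DBED procedure, not in scoring the SDQ. It makes a differential shift possible but gives no size or sign. If trained teachers scored lower, the artefact would reverse.
- **Parent report has no rater change, and the six-point primary endpoint stops before the break.** Both stand.

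A reader might go further and infer that the 10-wave slope cannot show a long-term effect at all. The sustained case refutes that: -0.83 against -0.8. A reader might also multiply the slope by five intervals and report an understated effect at wave 6. That leaves out the intercept: the fitted value there is -0.56 + 0.5(-0.0921) = -0.61, and wave 6 has its own six-point endpoint. Finally, a reader might infer that school teachers would be the trial's only raters unaware of allocation. The article says only "This is an open-label trial". It does not say what school teachers will be told, and parents may disclose the arm.

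**Conclusion.** The concern holds in a limited form. The 10-wave analysis spans a break whose date is known, and the stated rule for the shape of change ignores it. A single line serves well if the effect is sustained. It misleads if the effect fades (-0.39 fitted at wave 10 against a true 0). In teacher report it also misleads if an arm-differential rating shift ends at school entry (-1.31d on the change over the period).

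This rests on equally spaced waves, an even build-up to -0.8 at wave 6, and the inference that school teachers replace kindergarten teachers as raters. The significance and power figures rest further on assumed residual variances. The primary endpoint as defined in the Outcomes section is not touched. The point should be settled before any school-wave data are analysed.

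**What to change.** For any analysis that uses waves 7-10:

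1. Pre-specify a change of slope at school entry in each arm, in place of a data-driven choice of shape.
2. Define the secondary endpoint as the model-based arm difference at wave 10.
3. Analyse parent and teacher SDQ separately.
4. For parent report, also give wave 10 minus wave 6 as the measure of persistence.
5. For teacher report, analyse the school waves as their own arm contrast and do not join them to the kindergarten-teacher series, because there the end of DBED and the change of rater are confounded.

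A change of slope does not fit a loss that happens all at once: if -0.8 at wave 6 dropped straight to 0 at wave 7, it would read +0.20 at wave 10. A sensitivity analysis with an added arm-specific level step covers this.

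**Cost.** Wording, a few extra parameters and no new data. With 75 children per arm, complete waves and no cluster variance, the standard error of the fitted wave-10 difference rises from 0.85, 0.80 and 0.74 under the line to 0.87, 0.83 and 0.80 with the knot (residual variance 5, 10, 15), or 2-8%. Compared with testing the line's slope, the loss is larger: nine times the slope's standard errors of 0.040, 0.057 and 0.070 is 0.36, 0.51 and 0.63. The wave-10 estimate will be imprecise and should be reported with its interval.
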